# Health Facility hierarchy in Zambia

To avoid confusion, it is necessary to clarify terminology around health facilities. For the purposes of this document, the term rural health clinic (HC / RHC) will refer to all government run facilities that act as the primary location for health care service delivery and which are manned by professional health workers. In contrast, a rural health post (HP / RHP) is a satellite facility attached to an individual health centre that aims to expand health care access for a few key interventions, namely malaria testing and treatment. HP’s are predominantly manned by volunteer community health workers. The term health facility will refer to both HC’s and HP’s.

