| **Primary data collection & sampling method** | Sampling after the interventions will be used to determine malaria seropositivity in children under fifteen in each health center catchment population.  The routine government rapid reporting system will be used to determine confirmed malaria case incidence throughout the entire study area.  Longitudinal cohorts will be used to determine clearance and re-infection rates for each arm from a subset of individuals participating in reactive responses. |
| **Sample size** | - Simple random sample survey of children under fifteen in all health clinic catchments population : 8,000 - Routine reporting for malaria case incidence: ~130,000 (all ages) - Reactive responses in all areas: ~30,000 (all ages) - Re-infection / importation / serology in a subset of the study participants: ~9,000 (all ages) |
| **Statistical & analytic plan** | A difference-in-differences approach will be used to assess changes in both primary and secondary outcomes among intervention and control groups, using mixed effects logistic and Poisson models for the outcomes of parasite seropositivity and confirmed malaria incidence. Clearance and prevention of reinfection from areas receiving rapid responses will be determined through Poisson regression. Month-by-month estimates of effectiveness will be analyzed using the routine rapid reporting of confirmed malaria incidence.  We will estimate direct effects and spillover effects of the reactive, focal malaria interventions on malaria incidence and prevalence and assess whether effects vary by intervention coverage, distance to intervention, and time from incident case detection. We will then pool this data with other similar trials using fixed and random effects. |

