# Research Plan

## Study Design

The study design will be a cluster randomized trial comparing an enhanced strategy for malaria elimination (RFDA with DHAP) with the current strategy (RFTAT with AL). Impact evaluation will consist of: 1) community-based, cross-sectional measurement of malaria seropositivity in children aged ≥ 1 month and < 15 years through a random sample survey at the end (two years) of the intervention period; 2) longitudinal follow-up of a subset of individuals participating in reactive responses by a research team; and 3) detection of incident malaria cases and total outpatient attendance at health centers and health posts.

A total of sixteen health centers will be targeted in this RCT (Table 1). The proposed areas were selected from the 11 districts within Southern Province, Zambia that have successfully implemented RFTAT surveillance with the following criteria: a mean monthly incident malaria case load of < 25 and a mean test positivity during ongoing RFTAT of at least 5%. Where multiple health centers fulfilled the inclusion criteria, preference was given to those that are geographically close to one another (minimum 5km buffer to reduce contamination) and are accessible all year round. Selected health centres will be randomized to either control or intervention arms, with 8 health centers per arm (Figure 3).

| Organisation Unit | Confirmed Cases of Malaria (Sep ’13 – Aug ’14) | | | | Positivity Rate (%) during RFTAT |
| --- | --- | --- | --- | --- | --- |
|  | Clinic | Community | Total | Average cases per month |  |
| Chisekesi Rural Health Centre | 176 | 77 | 253 | 21 | 9.4 |
| Habulile Rural Health Centre | 133 | 109 | 242 | 20 | 9.3 |
| Katombora Health Post | 123 | 78 | 201 | 17 | 12 |
| Kazungula Health Post | 71 | 20 | 91 | 8 | 7.9 |
| Keemba Rural Health Centre | 58 | 89 | 147 | 12 | 6.8 |
| Mayoba Rural Health Centre | 46 | 37 | 83 | 7 | 9.4 |
| Moonde Rural Health Clinic | 0 | 214 | 214 | 18 | 8.3 |
| Mubanga Rural Health Centre | 77 | 139 | 216 | 18 | 5.3 |
| Mukwela Rural Health Centre | 86 | 157 | 243 | 20 | 7.8 |
| Munkolo Rural Health Centre | 42 | 76 | 118 | 10 | 6.9 |
| Musokotwane Health Post | 38 | 53 | 91 | 8 | 8.2 |
| Muzya Rural Health Centre | 40 | 83 | 123 | 10 | 9.9 |
| Nadezwe Rural Health Centre | 58 | 107 | 165 | 14 | 11.2 |
| Namwianga Urban Health Centre | 56 | 140 | 196 | 16 | 5.2 |
| Ngwezi Rural Health Centre | 11 | 169 | 180 | 15 | 8.3 |

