## Research Strategy by Aim

### Primary Aim

Compare the effectiveness of RFDA using DHAP with RFTAT using AL in achieving zero seropositivity in children under 15 years of age.

Hypothesis: RFDA with DHAP will be more effective in reducing malaria prevalence in the community than RFTAT using AL by clearing parasites from RDT-negative individuals with subpatent parasitemia and through the longer chemoprophylactic protection conferred by DHAP.

**Design**: Cluster randomized controlled trial in which eight health center catchment areas are randomized to RFTAT with AL (control arm) and eight health center catchment areas are randomized to RFDA with DHAP (intervention arm)

**Population**: Residents (under fifteen years of age) of a random selection of households in health center catchments within the intervention and control arms using satellite imagery to define the sampling frame

**Outcomes**: 1) malaria seropositivity measured at endline;

**Inclusion/Exclusion criteria:** All consenting individuals aged ≥ 1 month and < 15 years will be tested for parasite prevalence in the survey

**Procedures**: 1) randomization; 2) RFTAT with AL or RFDA with DHAP; 3) endline survey

**Assays**: Serological analysis of DBS collected during endline survey

**Analysis**: For the outcome of seropositivity, a comparison of seropositivity will be made between intervention and control areas and between children stratified into younger (aged ≥ 1 month to < 2 years), middle (aged ≥ 2 years to < 5 years), and older (aged ≥ 5 years and < 15 years). To account for correlated data at the cluster level, mixed effects regression models with the health center as a random intercept will be the primary analytic method to estimate the effectiveness of RFDA compared to RFTAT for the outcome of malaria prevalence as measured through seropositivity. Analyses will account for environmental factors, socio-economic status, housing construction, education level, and demographic measures of the population as well ITN coverage and indoor residual spraying.

### Secondary Aim 1

Compare the effectiveness of RFDA using DHAP with RFTAT using AL in reducing RDT confirmed malaria incidence through passive case detection at health facilities

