**Inclusion/Exclusion criteria:** All consenting individuals aged ≥ 1 month will be tested for parasite prevalence 0, 30 and 90 days following the reactive research response. Individuals to be included in the assessment of secondary aim 2 will have parasite measurements at 0, 30 and 90 days following the reactive research response.

**Procedures**: 1) reactive response; 2) follow-up visit at 30 days; 3) follow-up visit at 90 days

**Assays**: PCR for asexual parasites using DBS collected at 0, 30 and 90 days

**Analysis**: Parasite prevalence at 30 days and 90 days will be analyzed separately. Areas receiving a reaction will form the unit of analysis while malaria infections during returns to the areas receiving a reaction will be measured as a count variable. A mixed effects Poisson regression with the offset being the number of individuals providing filter paper with a DBS during the return to the areas receiving a reaction will be used to compare the effectiveness of RFDA v. RFTAT at clearing an area of malaria infections (30 days) and preventing reintroduction following the reactive response (90 days). A number of factors will be tested for acting as effect modifiers through a test for interaction including initial parasite prevalence at day 0 during the response, response coverage in the area, asset-based wealth index, vector control coverage of the area, age and demographics of the individuals living in the area, as well as environmental factors such as vegetation cover and topographical measures. A fixed effects regression approach, wherein the difference between the number of malaria-infected individuals at day 0 during the reaction and the number of malaria-infected individuals at day 30 and/or day 90 following the reaction may be used to assess how the malaria parasite reservoir changes following the reactive responses.

### Secondary Aim 3

Compare the cost-effectiveness of RFDA using DHAP with RFTAT using AL in reducing the prevalence of malaria in the community.

Hypothesis: RFDA will be more cost-effective in reducing malaria prevalence than RFTAT by clearing parasites from individuals with subpatent parasitemia, through the longer protective effect conferred by DHAP, and the cost savings of not using a diagnostic test (RDT).

**Design**: cluster randomized trial

**Population**: all residents of the health center catchment areas within the intervention and control arms

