**Inclusion/Exclusion criteria:** All individuals tested for malaria during the endline survey as well as during reactive research responses who have consented to further analyses of their dried blood spot sample.

**Procedures**: Sample collection from 1) reactive responses; 2) endline survey; genotyping of PCR-positive samples

**Assays**: Genotyping of *P. falciparum* genomes using PCR-positive DBS

**Analysis**: All malaria infections will be geo-referenced through data collection. Spatial variation in the genomic complexity and diversity will be estimated using the Geneland

^34^package in R

^35^ which uses Bayesian methodology to identify clusters of individuals with similar genotypes while accounting for spatial dependence of geo-referenced data. The procedure is capable of analyzing multivariate gene outcomes including SNPs. The number of separate genetic populations in the study area will be estimated and mapped; migrants (*P. falciparum* infections dissimilar genetically from others in nearby space) will be classified as imported malaria cases without onward transmission and will also be identified and mapped. The influence of a number of environmental factors on the spatial distribution of malaria parasites will be estimated. The enhanced vegetation index available through remotely sensed data will provide an indicator of adult mosquito habitat

^36,37^. A digital elevation model will be used provide an indicator for the propensity of an area to harbor mosquito breeding sites

^38–40^. We aim to utilise spatio-genetic methods that have been utilized in various aspects of ecology, but have not yet been applied to malaria epidemiology to understand transmission dynamics in the two arms

^41^.

Genetic complexity, defined as the number of genetically unique parasites found within health centre and health post catchments, will be compared between RFDA and RFTAT areas using a Poisson or linear regression depending upon the number of genetically unique parasites found. A number of factors will be tested including proximity of the area to the main road, wealth of the area, vector control coverage of the area, age and demographics of the individuals living in the area, as well as environmental factors such as vegetation cover and topographical measures.

### Secondary Aim 5

Assess the utility of serology to measure short-term changes in malaria transmission and evaluate malaria elimination programs

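### Secondary Aim 4 compares unique-parasite counts between arms by Poisson or linear regression with no health-centre or overdispersion term, although health centres are the randomised units

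*Protocol*

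**What the plan says.** Protocol section 2.1 (Study Design) sets the unit of allocation: "Selected health centres will be randomized to either control or intervention arms, with 8 health centers per arm".

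Section 2.8.5 (Secondary Aim 4) predicts that the diversity of locally transmitted parasites will end up lower where RFDA is given, which is a between-arm claim. Its outcome is genetic complexity, "defined as the number of genetically unique parasites found within health centre and health post catchments". The arms "will be compared between RFDA and RFTAT areas using a Poisson or linear regression depending upon the number of genetically unique parasites found". Area-level factors such as wealth, vector control and vegetation will also be tested. No random effect, overdispersion parameter or cluster-robust variance is named.

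The section on the health facility hierarchy says that a health post "is a satellite facility attached to an individual health centre".

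Other parts of the protocol do name such terms:
- Section 2.8.1 (Primary Aim): "mixed effects regression models with the health center as a random intercept will be the primary analytic method".
- Section 2.8.3 (Secondary Aim 2): "A mixed effects Poisson regression with the offset being the number of individuals providing filter paper with a DBS".
- Section 2.8.2 (Secondary Aim 1): a negative binomial model is offered as the alternative to Poisson.
- Project summary: "using mixed effects logistic and Poisson models for the outcomes of parasite seropositivity and confirmed malaria incidence". Genotype counts are not in that list.

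**The concern.** A trial that randomises 8 centres per arm must judge an arm difference against the variation between centres. The two models named for Aim 4 can miss that variation in different ways.

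- **Poisson.** The model sets the variance equal to the mean. Any real difference between centres in parasite diversity is extra variance that the standard error leaves out, whether there is one row per centre or several.
- **Linear.** The model estimates its residual variance from the data, so with one row per centre it is a valid 16-unit comparison. If a centre and its satellite posts enter as separate rows, they share an arm and a transmission setting but count as independent replicates.

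At stake is the prediction of lower diversity under RFDA. Standard errors that are too small could turn ordinary differences between centres into an apparent effect of the intervention on the parasite population.

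**Working it through.** **Inputs from the protocol.** There are 8 centres per arm (section 2.1). The inter-cluster variation is k = 0.5, range 0.3 to 0.7 (section 2.9, Table 3), given for seropositivity. Table 1 gives confirmed-case totals for 20 candidate facilities.

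**Assumptions.** The protocol does not give the number of unique parasites per centre (mu, taken as 3 to 50), the catchment rows per centre (J, taken as 1 to 6) or the CV of this outcome.

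**Step 1. What k means.** Aim 4 has no stated power or error rate to reproduce, but Table 3 shows how k is used. The Hayes-Bennett formula is c = 1 + (1.96 + 0.84)^2 x [p0(1-p0)/m + p1(1-p1)/m + k^2(p0^2 + p1^2)] / (p0 - p1)^2. With p0 = 0.05, m = 500, k = 0.5 and Table 3's 61.7% reduction (p1 = 0.01915):

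c = 1 + 7.849 x 0.000849 / 0.000952 = 8.0.

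The midpoint of Table 3 is reproduced, so k is a between-centre coefficient of variation.

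**Step 2. A proxy from the study's own facilities.** The 20 totals in Table 1 sum to 3,406, with mean 170.3 and variance 3,256. The variance is 3,256/170.3 = 19 times the mean. With Poisson noise removed, CV = sqrt(3,256 - 170.3)/170.3 = 0.33.

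**Step 3. Poisson option.** With no arm effect, the variance of a centre's count is mu(1 + k^2 mu), but the model assumes mu. The false-positive rate of a nominal 5% test is therefore about 2 x Phi(-1.96 / sqrt(1 + k^2 mu)). For k = 0.5 and mu = 20 the inflation is 1 + 0.25 x 20 = 6, and 2 x Phi(-0.80) = 0.42. Null simulations with gamma-distributed centre effects agree:

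| Unique parasites per centre | CV 0.33, formula | CV 0.33, simulated | CV 0.5, formula | CV 0.5, simulated |
|---|---|---|---|---|
| 5 | 11% | 11% | 19% | 18% |
| 10 | 18% | 17% | 29% | 29% |
| 20 | 27% | 27% | 42% | 42% |
| 40 | 40% | 39% | 55% | 55% |

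The number of rows per centre hardly changes these figures. With a CV of 0.15 the rate is 5-6% at 3 to 5 parasites and about 18% at 50. With no between-centre variation it is about 5% throughout.

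**Step 4. Linear option.** With J equal rows per centre, the intra-centre correlation is rho = (k^2 mu/J) / (1 + k^2 mu/J) and the design effect is 1 + (J-1)rho. For k = 0.5, mu = 20 and J = 3: rho = 1.667/2.667 = 0.625, the design effect is 2.25, and 2 x Phi(-1.96/1.5) = 0.19. Simulated rates at k = 0.5:
- one row per centre: about 5%;
- two rows: 8-16%;
- three rows: about 10-24% (mu from 3 to 40);
- four rows: 10-30% (mu from 3 to 50);
- six rows: 11-37% (mu from 3 to 50).

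**Step 5. Analysis at the randomised unit.** A t-test on 16 centre totals (14 df) stays at 4.4-5.4% in every scenario.

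**The case against.** - **Posts may not be extra rows.** Table 1 lists three of the candidate units themselves as health posts, so the phrase about health-centre and health-post catchments may simply name the randomised units. On that reading the linear option is already a 16-unit analysis with a nominal error rate. This stands, so nesting is a possibility and not an established fact. It does not rescue the Poisson option, which is inflated with one row per centre.
- **The CV is borrowed.** The 0.5 belongs to seropositivity and comes from a campaign in other districts, while these sites were screened for similar caseload. This stands as a limit on size. The Table 1 proxy, which reflects that screening, still gives 11-39%. It too is a proxy, because case totals are not genotype counts.
- **The outcome may vary less than assumed.** Distinct genotypes are capped by the infections genotyped, survey numbers per catchment are roughly equal, and area factors may absorb some between-centre variation. All of this could lower the rates. None of it replaces a cluster term.
- **The choice of model depends on the count.** If linear regression is kept for large counts, the highest Poisson rates would not arise. This is fair, but the wording sets no threshold.
- **An unseen statistical analysis plan could add the missing term.** It could, but the protocol names this model without one, while it names mixed models for other outcomes. Geneland's allowance for spatial dependence belongs to a separate mapping analysis.

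A reader might infer that either model gives a false-positive rate of 20-60%. The documents do not support that. The range fits only the Poisson option at a CV of 0.5 with about 5 or more unique parasites per centre.

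**Conclusion.** The point holds as a defect in the stated model. Section 2.8.5 sets out a randomised arm comparison whose named models make no provision for variation between the randomised centres, and the protocol makes that provision elsewhere. The Poisson option is anti-conservative under any extra-Poisson variation between centres. The linear option is so only if nested posts are separate rows.

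The size cannot be fixed from the document. The ranges given above depend on the assumed counts, rows per centre and CV, and they extend down to the nominal 5%. What is firm is the direction of the error, and that a comparison of centre-level values removes it.

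The consequence is moderate. This is one comparison within a largely descriptive secondary aim, and the primary analysis is unaffected. It should still be corrected, because the aim's hypothesis includes a difference between arms.

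**What to change.** In section 2.8.5, make the randomised health-centre catchment the unit of the arm comparison. Assign each post's parasites to its parent centre and count distinct genotypes over the combined area, so that one found at both is counted once. Then compare the 16 values by a t-test on 14 degrees of freedom, or by a permutation test that follows the actual randomisation.

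If facility rows are kept, state this and use a count model with a health-centre random intercept, an allowance for overdispersion (negative binomial, for example) and a small-sample reference on 14 degrees of freedom.

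The cost is one or two sentences and minor re-coding, with no new data. The price is wider intervals for this secondary comparison. If linear regression on one row per centre was always meant, the change only makes that explicit.

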## Survey Sample Size

The endline survey samples will provide malaria seropositivity parasite prevalence information for approximately 500 children per RHC catchment area (150 ≥ 1 month and < 2 years; 150 ≥ 2 years and < 5 years; 200 ≥ 5 years and < 15 years). Seropositivity in control arms is assumed to be at least equal to a parasite prevalence (as measured by RDT) of 5%. An inter-cluster variation of 0.5

^43^, was found in the mass screening and treatment campaign in the districts adjacent Lake Kariba and was used for this sample size calculation. Including 8 health centers per intervention arm would allow for detection of a 64.5% relative difference between intervention arms with 80% power and 95% specificity (decrease from 5% seropositivity to 1.78 %).

Table 3 shows a sensitivity analysis of the detectable relative difference in intervention arms when varying the assumptions for seropositivity and inter-cluster variation with the midpoint estimate in bold.

Table 3 - Sensitivity analysis of detectable relative difference in seropositivity between intervention arms when varying seropositivity and the inter cluster variation while assuming 8 health centers per intervention arm and 500 children sampled per health center catchment. Figure in bold represents best estimates of parameters.

| Inter cluster variation | Seropositivity | | | | |
| --- | --- | --- | --- | --- | --- |
|  | 1% | 2.5% | **5%** | 7.5% | 10% |
| 0.3 | 64.5% | 50.7% | 44.6% | 42.3% | 41.1% |
| 0.4 | 69.7% | 58.0% | 53.1% | 51.4% | 50.4% |
| **0.5** | 75.7% | 65.7% | **61.7%** | 60.3% | 59.6% |
| 0.6 | 82.3% | 73.7% | 70.4% | 69.2% | 68.6% |
| 0.7 | 89.5% | 81.9% | 79.1% | 78.1% | 77.6% |

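### The detectable difference in the text of section 2.9 (64.5%, 5% to 1.78%) contradicts Table 3 (61.7%) for the same inputs, and the stated design does not give it at 80% power

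*Protocol*

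**What the plan says.** Section 2.9 (Survey Sample Size) sets out the power calculation for the primary outcome, seropositivity in children under fifteen at endline. Its inputs are:

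- Control-arm level: "Seropositivity in control arms is assumed to be at least equal to a parasite prevalence (as measured by RDT) of 5" percent.
- Between-cluster variation: "An inter-cluster variation of 0.5", with a reference to the Hayes and Bennett sample size paper.
- Cluster size: "approximately 500 children per RHC catchment area".
- Clusters: eight health centers in each arm, as in section 2.1 ("with 8 health centers per arm").

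From these the text claims "detection of a 64.5% relative difference between intervention arms with 80% power and 95% specificity (decrease from 5% seropositivity to 1.78" percent).

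Table 3 then varies seropositivity and inter-cluster variation, "assuming 8 health centers per intervention arm and 500 children sampled per health center catchment". Its row for variation 0.5 reads "0.5 | 75.7% | 65.7% | 61.7% | 60.3% | 59.6" percent, for seropositivity of 1%, 2.5%, 5%, 7.5% and 10%. The 61.7% under 5% is bold, and the caption explains bold as the best estimates of the parameters.

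**The concern.** The sentence and the bold cell describe one scenario and give two answers, 64.5% and 61.7%. Nothing in section 2.9 separates the two cases: clusters, children per cluster, control level and variation are all the same. The value 64.5% does occur in Table 3, but only at variation 0.3 and seropositivity 1%, which is not the base case.

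This is the only power statement in the protocol, and it concerns the primary aim. A reader who wants to know what effect the trial was sized to detect finds two figures. The 80% power can belong to only one of them under the stated inputs. If the text figure came from less favorable inputs that are not disclosed, the table would be too optimistic throughout.

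**Working it through.** **Inputs (section 2.9, and section 2.1 for the arms).** Control proportion p0 = 0.05; coefficient of variation k = 0.5; children per center m = 500; centers per arm c = 8; power 80%. I read "80% power and 95% specificity" as 80% power at a 5% significance level. Sidedness is not stated; I take two-sided and test that choice against Table 3. No allowance for non-response is stated, so none is applied.

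**Formula (Hayes-Bennett, unmatched proportions).**

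c = 1 + (1.96 + 0.84)² × V / (p0 − p1)²

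V = p0(1 − p0)/m + p1(1 − p1)/m + k²(p0² + p1²)

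The squared normal quantiles come to 7.849 before rounding.

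**Step 1: reproduce Table 3.** Solving for p1 with c = 8 and m = 500 gives these relative reductions (protocol figure in brackets where the first decimal differs):

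| k | 1% | 2.5% | 5% | 7.5% | 10% |
|---|---|---|---|---|---|
| 0.3 | 64.4 [64.5] | 50.7 | 44.6 | 42.3 | 41.1 |
| 0.4 | 69.7 | 58.0 | 53.1 | 51.3 [51.4] | 50.4 |
| 0.5 | 75.7 | 65.7 | 61.7 | 60.3 | 59.6 |
| 0.6 | 82.3 | 73.7 | 70.3 [70.4] | 69.2 | 68.6 |
| 0.7 | 89.5 | 81.9 | 79.1 | 78.1 | 77.6 |

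The largest gap over the 25 cells is 0.07 percentage point. The table itself therefore identifies the method: two-sided 5%, 80% power, one added cluster, 500 children.

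**Step 2: base case.** The solution is p1 = 0.01914, a reduction of 61.7%. Check:

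- V = 0.0000950 + 0.0000375 + 0.25 × (0.0025 + 0.000366) = 0.000849
- (p0 − p1)² = 0.03086² = 0.000952
- c = 1 + 7.849 × 0.000849 / 0.000952 = 8.0

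**Step 3: the figure in the text.** At p1 = 0.0178:

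- V = 0.0000950 + 0.0000350 + 0.25 × (0.0025 + 0.000317) = 0.000834
- (p0 − p1)² = 0.0322² = 0.001037
- c required = 1 + 7.849 × 0.000834 / 0.001037 = 7.31
- Power with 8 centers = Φ(√(7 × 0.001037 / 0.000834) − 1.96) = Φ(0.99) = 0.839

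A noncentral t calculation with 14 degrees of freedom gives 0.834.

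**Step 4: could another method give 64.5%?** For the base-case inputs:

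| Variant | Relative reduction |
|---|---|
| No added cluster | 58.4% |
| Two added clusters | 65.8% |
| One-sided, 80% power | 55.9% |
| One-sided, 90% power | 64.0% |
| Two-sided, 90% power | 69.6% |
| Design-effect form, one added cluster | 66.0% |
| Design-effect form, none added | 62.5% |
| Noncentral t, 14 df | 62.0% |
| t quantiles, 14 df, with c − 1 | 65.5% |

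None gives 64.5% with 1.78%. If the formula is kept and one input is changed, 64.5% needs about 290 children per center, or k of about 0.53, or p0 of about 3%, or power of about 84%.

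**Step 5: rounding slip?** 5% × (1 − 0.645) = 1.775%, so the two numbers in the sentence agree with each other. The difference from the table is not a rounding error between them.

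**The case against.** The strongest reply is that the error is harmless and the sentence is, read literally, true. It errs on the safe side, because the design has more than 80% power for the effect in the text. Centers are whole units, so 7.31 rounds up to 8, and eight centers do detect a 64.5% reduction with at least 80% power. The number of centers, the number of children, the outcome and the analysis do not change. The 2.8-point gap is also small beside the spread of Table 3 at 5% seropositivity (44.6% to 79.1%), and the caption tells the reader which cell is the base case.

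Much of this stands. The discrepancy is conservative and does not by itself weaken the trial. The rounding argument does not rescue the sentence, though. Table 3 solves for exactly 8 centers, and the text offers 64.5% as what 8 centers give at 80% power, so on the protocol's own convention the figure is 61.7%. Seven centers would give 65.8%, so 64.5% is not a whole-center answer either.

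A second point also stands: the document does not show where 64.5% came from. Section 2.5 samples households and tests all consenting children in them, so an undisclosed allowance for household clustering is possible. About 290 effective children out of 500 would be a design effect near 1.7. That is conjecture; the other single-input changes in step 4 fit as well. It is a reason not to assume without checking that the sentence, and not the table, is wrong.

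**Conclusion.** The point holds. For 8 centers per arm, 500 children per center, 5% seropositivity and variation 0.5, the text and Table 3 of section 2.9 disagree by 2.8 percentage points of relative difference (64.5% against 61.7%; 1.78% against 1.91% in the intervention arm). The stated inputs support the table. At the text's effect, power is about 84%.

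This rests on the two-sided Hayes-Bennett formula with one added cluster, which the protocol cites and which its table confirms, and on the inputs as printed. The practical consequence is limited: the error is conservative, and no larger sample is needed if the sentence is the mistake. It still has to be corrected, because it is the stated design target for the primary outcome. The alternative, that the table omits an allowance used in the text, would make Table 3 too optimistic.

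**What to change.** Go back to the calculation behind 64.5% and reconcile the two figures in section 2.9.

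- If it was meant to use the stated inputs, change the text to a 61.7% relative difference (5% to 1.91%) at 80% power.
- If it used other inputs, such as a household design effect or a smaller effective cluster size, state them and recompute all of Table 3 on that basis.

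In the same edit, replace the term specificity with a two-sided 5% significance level, which is what Table 3 uses. The first route costs one sentence. The second costs a sentence and a recomputed table. Correcting the sentence requires no change to the number of centers or children.
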